### 2.3 Blinding and randomization

Considering that the subjects in our study will be aware of what kind of chemotherapy they receive, we will not utilize the double-blind method [17]. To reduce potential bias and ensure fair allocation of participants, we designed blocks of size four and randomly assigned patients to either the PTC adjuvant chemotherapy group or the traditional chemotherapy group at a 1:1 ratio. Stratification was performed according to the surgical center [18].

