#### 2.2.2 Exclusion criteria.

The exclusion criteria are as follows: 1) patients with distant metastases; 2) patients unable to obtain tumor samples; 3) pregnant and lactating women; 4) patients with poor compliance; 5) patients with severe cardiovascular and cerebrovascular complications unable to receive chemotherapy or targeted therapy; 6) patients previously diagnosed with other malignant tumors; 7) patients with severe mental and neurological disorders; and 8) patients deemed unsuitable for participation in this study by researchers.

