### 2.4 Intervention

We plan to include 200 patients for analysis, with 100 in the experimental group and 100 in the control group. Both groups will undergo PTC drug sensitivity testing and whole exome sequencing (WES). For the experimental group, doctors will select adjuvant chemotherapy regimens on the basis of the PTC drug sensitivity test results. For the control group, doctors will determine adjuvant chemotherapy strategies on the basis of their clinical experience. The PTC drug sensitivity and WES results will be documented for humanitarian treatment reference after the study concludes or if patients withdraw from the study.

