## Time points/timeline, trial status, and publication plan

Recruitment for this RCT commenced in 2021, with the first patient enrolled on November 9, 2021. The recruitment was initially planned to be completed by 2024. However, due to the impact of the COVID-19 pandemic, recruitment for this study has been significantly delayed, and the enrollment deadline has been extended to September 1, 2025. Publication based on Protocol Version 1.0: 28 September 2021. At the time of publication, all sites are open to recruitment.

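### A single block size of four within each centre, in a trial without blinding, lets a centre that knows the block size deduce about 30 to 33% of its allocations in advance

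*Protocol article*

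**What the plan says.** All references are to the protocol article.

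- **Allocation (section 2.3).** One block size is given: "we designed blocks of size four and randomly assigned patients". The arms are "either the PTC adjuvant chemotherapy group or the traditional chemotherapy group at a 1:1 ratio", so each block holds two of each. On strata: "Stratification was performed according to the surgical center". No variation in block size is mentioned.
- **Blinding (sections 2.3 and 2.4).** The article states that "we will not utilize the double-blind method". In the experimental arm "doctors will select adjuvant chemotherapy regimens on the basis of the PTC drug sensitivity test results"; in the control arm "doctors will determine adjuvant chemotherapy strategies on the basis of their clinical experience". The treating doctors therefore know each patient's arm.
- **Entry (sections 2.2 and 2.2.2).** Consent is signed and tissue taken before enrolment. Selection against the entry criteria follows once the surgical pathology report is available. The exclusions include poor compliance and "patients deemed unsuitable for participation in this study by researchers".
- **Status (timeline section).** The first patient was enrolled on 9 November 2021 and the deadline was extended to 1 September 2025. "At the time of publication, all sites are open to recruitment". The number enrolled is not given.

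**The concern.** Blocking within centre keeps the arms balanced locally. The price is that the end of each block is determined by its beginning. That price is small when staff do not know the block size or cannot see earlier assignments. Here assignments are visible by design, and the only block size named is short and now in print.

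Predictability matters only if it can affect who enters, and the article leaves room for that. Pathology, which bears on prognosis, is known when eligibility is decided, and two exclusions rest on judgement. Someone expecting a particular arm next could pass over a candidate or change the order in which two candidates are entered.

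At stake is the comparability of the arms on the primary endpoint, 3-year disease-free survival. A tilt in favour of the PTC arm would make noninferiority easier to claim; a tilt the other way would make it harder. The document gives no reason to expect one direction over the other.

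**Working it through.** **Inputs.** Block size 4, 1:1 allocation, strata by surgical centre (section 2.3); 9 hospitals (section 2.1); 200 patients (section 2.7.1). The article states no figure for predictability, so there is none to reproduce.

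**Step 1: certain allocations per block.** An assignment is certain once one arm has used both its places in the block. The six equally likely orders give:

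| Order | Certain assignments |
|---|---|
| AABB | 2 |
| BBAA | 2 |
| ABAB | 1 |
| ABBA | 1 |
| BAAB | 1 |
| BABA | 1 |

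Mean = (2 + 2 + 1 + 1 + 1 + 1)/6 = 8/6 = 1.33 of 4, or 33.3%. The fourth place is always certain and the third is certain with probability 1/3. Cross-check: the expected final run in a block of 2m is 2m/(m + 1); with m = 2 this is 4/3.

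**Step 2: best-guess success.** Guess the arm with more places left, and toss a coin when they are equal.

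- Place 1: 0.5.
- Place 2: 2/3.
- Place 3: right with certainty in 1/3 of blocks and a coin toss in the other 2/3, so 1/3 + 2/3 × 0.5 = 2/3.
- Place 4: 1.

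The sum is 2.833, and 2.833/4 = 70.8%, against 50% by chance.

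**Step 3: scale to the trial.**

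- All blocks complete: 200/3 = 66.7 patients (33.3%).
- Even spread (assumed: seven centres with 22 and two with 23): a centre with 22 has 5 complete blocks plus 2 patients, so 5 × 4/3 = 6.67 certain. A centre with 23 adds a third place, so 6.67 + 0.33 = 7.0. Total 7 × 6.67 + 2 × 7.0 = 60.7 (30.3%).
- Other spreads: relative to one third of its patients, a centre loses 0, 1/3, 2/3 or 2/3 of a certain assignment when its last block holds 0, 1, 2 or 3 patients. The most that nine centres can lose is 9 × 2/3 = 6. The expected total therefore lies between 60.7 and 66.7 however patients are distributed.

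**Step 4: what other block schemes would do.** Fixed sizes are by enumeration. Mixed sizes are by simulation (20,000 runs of 24 patients) of an observer who knows which sizes are in use but not their order.

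| Scheme | Certain in advance | Best guess right |
|---|---|---|
| Fixed 4 | 33.3% | 70.8% |
| Fixed 6 | 25.0% | 68.3% |
| Fixed 8 | 20.0% | 66.6% |
| Random 4 and 6 | about 5.8% | about 68.7% |
| Random 4, 6 and 8 | about 2.4% | about 67.3% |

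Varying the block size removes most of the certainty but little of the guessing advantage.

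**Step 5: what a baseline check could detect.** The 61 to 67 predictable assignments give roughly 30 to 33 per arm. Suppose a binary prognostic factor differs 50% v 70% between arms (assumed). SE = √(0.25/n + 0.21/n), which is 0.124 at n = 30 and 0.118 at n = 33. Power = Φ(0.20/SE − 1.96), or about 37% to 40%. A clean result would reassure only a little.

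**The case against.** **The deduction needs knowledge that sites may not have had.** This stands in part. The figures apply only to someone who knows the block size and keeps track of earlier allocations at the centre. Whether sites were told the block size in the full protocol of September 2021 is not shown. Publication itself exposes only patients entered afterwards.

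**Concealment may be described in the full protocol.** That is fair, and nothing here relies on the article's silence. However, hiding the next assignment in a central system does not prevent deduction from past assignments when the block size is known.

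**The exclusions are ordinary wording, and consented candidates who were not entered can be traced.** Both are true. Traceability helps the remedy, but it does not remove the opportunity.

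**Few slots may remain, and used blocks cannot be changed.** This stands, and it limits the severity. It does not defeat the point: the article reports every site still recruiting, and the analysis step applies whatever number remains.

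**Stronger readings a reader might infer.** One is that a third of this trial's allocations were in fact known and exploited. The document contains no evidence of selective entry. Another is that the false-noninferiority rate is raised by some definite amount. Any such figure needs an assumed prognostic tilt running in one direction across centres. The document supports neither its size nor its direction, so no figure is given here.

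**Conclusion.** The point holds as an avoidable exposure in the design. It is not an error of calculation, and it does not show that the comparison is biased. For an informed observer at a centre, an average of 1.33 of 4 assignments is certain: 30 to 33% of patients, or about 61 to 67 of 200. This rests on three conditions: one block size throughout, blocks run separately in nine centres, and knowledge of the block size and of earlier assignments. The article states or directly implies the first two and the visibility of past assignments. Knowledge of the block size before publication is possible but not shown. Severity is low to moderate, because the number of patients still to be randomised is not stated.

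**What to change.** **For all remaining randomisations**

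1. Replace the fixed blocks with randomly varying sizes, for example 4 and 6, not disclosed to sites.
2. Record the eligibility decision for every consented candidate, with the reason for any non-entry, before the allocation is released. If the full protocol already requires this, confirm it. The step is essential, because varying the blocks leaves best-guess success at about 69%. It cannot stop someone acting on a guess, but it makes selective entry visible.

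**For patients already entered**

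3. Specify, before outcomes are examined, a sensitivity analysis of 3-year disease-free survival adjusted for recorded baseline stage and age. It can correct only for measured differences.
4. Describe baseline balance between arms by predictable v unpredictable block position, stating its low power. Report candidates who were eligible but not randomised, by centre.

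**Cost.** A short amendment to the ethics committee and new lists for the remaining slots at nine sites. Within-centre imbalance could reach 3 instead of 2. Steps 3 and 4 use baseline data and allocation records that the trial should already hold. If recruitment has closed, only these two steps apply.

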## 1 Background

Colorectal cancer (CRC) is a common gastrointestinal malignancy that seriously endangers human health. According to cancer statistics 2023 [1], CRC has become the third most common cancer in terms of both incidence and mortality rates. Approximately 25–30% of stage II CRC patients experience recurrence and metastasis within 5 years after surgery, whereas approximately 50–60% of stage III CRC patients experience recurrence and metastasis within 5 years after surgery [2,3]. In addition, 45–50% of patients with stage II-III disease develop liver metastases within two years after primary resection [4,5]. As the main adjuvant treatment for CRC surgery, multiple international clinical studies have shown that surgery combined with adjuvant chemotherapy can achieve a total 5-year survival rate of 60–70% and a total 5-year disease-free survival rate of 55–65% for high-risk stage II and stage III patients [6,7].

However, CRC is a malignant tumor with significant heterogeneity [8,9], and there are significant individual differences in drug sensitivity among patients. Even patients with the same pathological type and clinical stage who receive the same treatment plan have different prognoses and outcomes [10]. The selection of adjuvant chemotherapy regimens for different subgroups of patients remains controversial. Therefore, constructing a model that can accurately predict drug efficacy and guide personalized treatment for patients is one of the strategies for achieving precision treatment of CRC. Scientists have been dedicated to developing in vitro models for drug sensitivity testing over the past century, including cell lines, primary tumor cells [11], patient-derived organoids (PDOs) [12], and patient-derived tumor xenograft (PDX) mice [13]. However, owing to issues such as standardization, accuracy, and cycle, these methods have certain limitations in clinical application and struggle to achieve true clinical translation.

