## 2 Methods and design

### 2.1 Study overview

This multicenter randomized controlled trial (RCT) will be conducted at 9 tertiary hospitals: Peking Union Medical College Hospital, Tianjin People’s Hospital, Chinese PLA General Hospital, Beijing Chaoyang Hospital Affiliated with Capital Medical University, Huazhong University of Science and Technology Tongji Medical College Affiliated Union Hospital, Dalian Medical University Affiliated First Hospital, The Second Affiliated Hospital of Harbin Medical University, Cancer Hospital of Xiangya Medical College Central South University, and Peking University International Hospital. The study was designed following the Standard Protocol Items: Recommendations for Interventional Trials (SPIRIT) statement [16] (Fig 1). Participants who meet the inclusion criteria will be randomly assigned at a 1:1 ratio to either the PTC-guided adjuvant chemotherapy group (experimental group) or the traditional chemotherapy group (control group). These participants will then receive different interventions and undergo evaluations throughout the entire duration of the trial (see Fig 2 for a depiction of the study flow). Baseline data will be collected from participants at the beginning of the trial, followed by follow-up assessments at specific intervals. The primary endpoint of the study is the 3-year disease-free survival rate (3yDFS). Through this study, we aim to evaluate the results of PTC drug sensitivity testing in comparison with clinical outcomes, assess the consistency between the results of this technological platform and clinical prognosis, and provide a valuable reference for achieving individualized and precise treatment for CRC patients, thereby improving clinical benefits.

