#### 2.2.1 Inclusion criteria.

The inclusion criteria are as follows: 1) patients with histologically confirmed CRC; 2) baseline clinical stage of cT3-4N0M0 or cTanyN + M0; 3) CRC patients requiring adjuvant treatment after radical surgery and not receiving neoadjuvant treatment; 4) at least one evaluable tumor lesion; and 5) Eastern Cooperative Oncology Group (ECOG) performance status ≤ 2.

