#### 2.7.3 Statistical methods.

Local recurrence is defined as tumor recurrence in the lumen or in the mesorectum and must be confirmed by a pathological biopsy. A distant metastasis is defined as a metastasis that is discovered in the liver, lung, bone, or other sites by CT, MRI, or radionuclide scanning, with or without pathological examination. Disease-free survival (DFS) is defined as the absence of local recurrence, distant metastasis, and death from any cause. Overall survival (OS) is defined as the absence of death from any cause. The duration of follow-up will be calculated from the date of surgery to the event of interest or the last follow-up date.

To determine the consistency between the PTC drug sensitivity results and clinical outcomes, the following methods will be employed (Table 2): positive consistency rate = a/(a + c) × 100%; negative consistency rate = d/(b + d) × 100%; overall consistency rate = (a + d)/(T1) × 100%; sensitivity = a/(a + b) × 100%; and specificity = d/(b + d) × 100%.

**Table 2 pone.0326760.t002:** Consistency test of recurrence and metastasis cases.

Drug sensitivity test	Clinical efficacy		Sum
	CR + PR	SD + PD	
**Effective**	a	B	a + b
**Invalid**	c	D	c + d
**Sum**	a + c	b + d	T1

The results will be presented as median values or means ± standard deviations for continuous variables and as numbers (percentages) for categorical variables. The t test and Wilcoxon rank sum test will be used to compare continuous variables, and chi-square analysis/Fisher’s exact test will be used to compare categorical variables. Survival analysis will be conducted using the Kaplan-Meier curves. Log-rank test to compare the primary endpoint between different arms in the presence of censoring. A P value of 0.05 or less is considered statistically significant. All the statistical tests will be two-sided. All analyses will be performed using SPSS Version 26.0 (SPSS Inc., Chicago, IL).

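### The primary test named in the article uses neither centre nor stage: a small, cheaply recovered loss of efficiency, not a bias

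*Protocol article*

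**What the plan says.** **Allocation.** Section 2.1: "This multicenter randomized controlled trial (RCT) will be conducted at 9 tertiary hospitals". Section 2.3: "we designed blocks of size four and randomly assigned patients", at 1:1, and "Stratification was performed according to the surgical center". No other stratification factor is given.

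**Analysis.** Section 2.7.3 gives, for the primary endpoint, "Log-rank test to compare the primary endpoint between different arms in the presence of censoring", and adds "All the statistical tests will be two-sided". The other methods listed there are Kaplan-Meier curves, the t test, the Wilcoxon test and chi-square or Fisher's exact test. No regression model or stratified test appears.

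**Stage.** Section 2.2.1 admits node-negative and node-positive patients together: "baseline clinical stage of cT3-4N0M0 or cTanyN + M0". The expected mix is not stated. Section 1 gives the prognosis of each group: "Approximately 25–30% of stage II CRC patients experience recurrence and metastasis within 5 years after surgery", and "approximately 50–60% of stage III CRC patients experience recurrence and metastasis within 5 years after surgery".

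**Design figures.** Section 2.7.1 describes a non-inferiority trial with two-sided alpha 0.05, 80% power, 75% 3-year DFS, a 20-point margin, 74 per group, and 100 per group after 20% dropout.

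**Availability of stage.** Under section 2.2, clinical and pathological features are recorded for every enrolled patient, and patients are selected once surgical pathology is known. Pathological stage can therefore serve as a baseline covariate.

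**The concern.** Two things do not fit together. The one factor used to balance the arms, centre, is absent from the test that compares them. And the one factor for which the article itself reports a roughly two-fold difference in outcome, stage, is used nowhere.

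When a prognostic baseline factor is left out, its variation between patients stays in the error term, so the confidence interval is wider than it need be. If the arms turn out unequal on stage, the unadjusted estimate is also moved in a known direction. The allocation can no longer be changed for patients already enrolled since November 2021, but the analysis still can. Because the trial is open-label, an adjustment introduced after an imbalance has been seen would look post hoc. The question is how much this matters at 100 per arm.

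**Working it through.** **1. Reproduce the planned sample size.** With equal 3-year DFS of 75%, margin 0.20, one-sided 0.025 and 80% power:

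n = 2 × 0.75 × 0.25 × (1.960 + 0.842)² / 0.20² = 73.6, so 74 per arm, as stated. Allowing for dropout, 74 / 0.8 = 92.5, so 93; the plan rounds up to 100. The calculation uses neither centre nor stage.

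**2. Stage contrast (section 1).** 50/25 = 2.0 and 60/30 = 2.0. The extremes of the quoted ranges are 50/30 = 1.67 and 60/25 = 2.4. These are 5-year recurrence figures.

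**3. Variance explained by stage at 3 years.** Hold the overall event rate at the planned 25%. Let f be the stage III share and r the stage III:II ratio, both carried to 3 years by assumption:

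- e₂ = 0.25 / (1 − f + f·r), and e₃ = r·e₂
- R² = f(1 − f)(e₃ − e₂)² / (0.75 × 0.25)

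For f = 0.5 and r = 2: e₂ = 0.167, e₃ = 0.333, R² = 0.25 × 0.167² / 0.1875 = 0.037. The required n becomes 73.6 × (1 − 0.037) = 70.9, so 71 per arm.

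The shift column is 1.96 × √(2f(1 − f)/100) × (e₃ − e₂), at 100 per arm:

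| f | r | R² | n per arm | Shift at 95% imbalance (points) |
|---|---|---|---|---|
| 0.3 | 1.67 | 2.2% | 72 | 1.8 |
| 0.3 | 2.0 | 4.1% | 71 | 2.4 |
| 0.3 | 2.4 | 6.8% | 69 | 3.1 |
| 0.5 | 1.67 | 2.1% | 73 | 1.7 |
| 0.5 | 2.0 | 3.7% | 71 | 2.3 |
| 0.5 | 2.4 | 5.7% | 70 | 2.9 |
| 0.7 | 1.67 | 1.4% | 73 | 1.4 |
| 0.7 | 2.0 | 2.4% | 72 | 1.9 |
| 0.7 | 2.4 | 3.5% | 71 | 2.3 |

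**4. Power.** Power = Φ(0.20/SE − 1.96), with SE = √(2 × variance/n). In the central case, adjustment raises power from 83.2% to 84.5% at 80 evaluable per arm, and from 90.4% to 91.4% at 100. Over the whole grid the gain is 0.4 to 2.5 points.

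**5. Chance imbalance.** At f = 0.5 and 100 per arm, the SD of the difference in stage III share is √(2 × 0.25/100) = 7.1 points. The 95% range is ±13.9 points, and a gap above 10 points has probability 15.7%. The shift is 13.9 × 0.167 = 2.3 points, against an unadjusted SE of √(2 × 0.1875/100) = 6.1 points. With 80 per arm the largest shift on the grid is 3.5 points.

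This is the same effect as step 3. One SD of imbalance shifts the estimate by 7.07 × 0.167 = 1.18 points, and (1.18/6.12)² = 0.037, which is the R² already found.

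**6. Simulated log-rank test.** N = 200, nine centres of equal expected size, blocks of four, half stage III, r = 2, 20% dropout by 3 years, 6,000 runs per scenario. Null rejection of the unstratified test was 4.8–4.9%. Power at a hazard ratio of 0.45, chosen only to compare tests:

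| Strata | No centre effect | Centre log-hazard SD 0.3 |
|---|---|---|
| None | 60.7% | 60.1% |
| Centre | 60.3% | 59.9% |
| Stage | 61.7% | 60.9% |
| Centre × stage | 58.6% | 58.6% |

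Monte Carlo error per figure is about √(0.6 × 0.4/6000) = 0.6 points.

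**The case against.** The strongest objection is that the article is silent rather than wrong. It never calls the log-rank test unstratified, it condenses a longer protocol, and strata or covariates are often left to a SAP. That stands as a limit on the wording: the article names none, which does not prove that none are planned. It does not remove the point, because section 2.7.3 fixes a named primary test within a list of wholly unadjusted methods, and a better choice is available at almost no cost.

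Three stronger readings are tempting and are not supported.

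- **That the result would be biased or the error rate wrong.** Random stage imbalance is part of the sampling error that the unadjusted test already allows for, and simulated type I error stays near 5%.
- **That the loss is about 8% of variance (17 of 200 patients), with shifts of up to a fifth of the margin.** Those figures follow from the 5-year midpoints, 27.5% and 55%. At a 50:50 mix they give R² = 7.8% and a 2-SD shift of 14.1 × 0.275 = 3.9 points. But they imply 41% events, whereas the endpoint is 3-year DFS planned at 25%. Converting them to 3 years with constant hazards gives 17.5% and 38.1%, R² of about 5%, still with more events (27.8%) than planned.
- **That ignoring centre inflates the standard error.** This matters only if centre is prognostic. The document does not say that it is, and stratifying by centre brought no gain in simulation.

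The stage contrast is itself uncertain. Section 1 describes stage II patients in general, whereas the trial enrols those needing adjuvant treatment, which section 3 limits for stage II colon cancer to high-risk features. The true ratio may be below two, and the gain smaller still.

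**Conclusion.** The point holds as a low-cost recommendation. Centre is in the randomisation but not in the named test, and stage is in neither, despite a two-fold difference in 5-year recurrence on the article's own figures. The price is about 4% of the outcome variance, or 74 versus 71 patients per arm; the cushion between the 93 needed and the 100 planned is already larger than that. Neither the validity of the test nor the adequacy of the sample size is called into question on this ground.

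These sizes rest on an unstated stage mix (30–70% stage III tried), the 5-year ratio carried to 3 years, 75% DFS overall, and 3-year DFS treated as a binary outcome. Confidence is high about what the article names, and moderate about the size. The case for including centre is agreement with the randomisation, not power.

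**What to change.** Prespecify, before any comparison by arm:

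- **Primary estimate:** the difference in 36-month DFS adjusted for pathological stage II/III. One option is the Kaplan-Meier difference within each stage, weighted by the pooled stage shares, with a confidence interval compared with the 20-point margin. A log-rank test does not by itself address that margin, so an estimator of the 36-month difference has to be written anyway; adjusting it for stage adds little.
- **Centre:** reflect it in the analysis, pooling small centres by a rule stated in advance. Avoid centre-by-stage cross-strata, which cost about 1.5 to 2 points of power in simulation.
- **Sensitivity analysis:** report the unadjusted comparison alongside.

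The cost is SAP wording, minor extra analysis work and the pooling rule. No new data are needed, and neither the sample size nor the randomisation changes. If the SAP already contains this, a sentence saying so in the protocol is enough.
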